The calculation of insulin doses will be performed based on the individual’s ICR counted per 10 g of CHO. The normal bolus will be calculated as 6 × ICR, and the Super Bolus will be calculated as 150% × 6 × ICR, with the suspension of basal insulin for 2 h after the delivered prandial bolus. The CRF containing the protocol for both groups, the personal data, and the calculations concerning insulin doses will be filled in for both groups on the first day. A closed envelope with patient allocation will be attached to the CRF. In the next 2 days, patients will eat h-GI breakfast, and the bolus order will depend on the allocation group. Nurses who will not be involved in the study will administer the right type of bolus. To ensure that the study protocols will not be mixed up and remain blind, the nurse administering the premeal bolus will check the allocation in the envelope and will provide the appropriate type of bolus. The study duration per day is planned for 3 h. No additional meals, snacks, or correction boluses are allowed during this time. An observation time of 3 h is defined as an approximation of the total lasting hypoglycemic effect after a subcutaneous insulin bolus dose. The capillary blood glucose level will be measured with a Contour® Plus Link Meter at 0, 30, 60, 90, 120, 150, and 180 min after insulin administration with a continuously working monitoring system. There is a high possibility that rapid glycemic fluctuations will be observed after an h-GI meal. Therefore, the blood glucose level can be checked with both the CGM and glucometer to obtain the highest accuracy of glycemic level at the specified time point. Caregivers and patients will also be instructed to report symptoms of hypoglycemia with additional glycemia measurements. Hypoglycemia will be defined as the glucose level below or equal to 70 mg/dl (≤ 3.9 mmol/l), which is treated as a clinical hypoglycemia alert according to the ISPAD Guidelines 2018.^1^ If hypoglycemia occurs, the patient will receive 0.3 g/kg of glucose/saccharose. After 15 min, the glucose level must be controlled again. If hypoglycemia persists, the patient will receive the next dose of glucose/saccharose, until a glucose level over 70 mg/dl is achieved. The presence of hypoglycemia will not suspend the study process, and SMBG will be performed as it is established. The records from the CGM will be registered using the Medtronic Care Link Pro Software and discussed with the patients for educational purposes. The participants may discontinue the trial at any point in time without giving a reason. The researchers will make every effort to supervise, educate, and regularly control the patients to provide the proper study process.

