### Statistical analysis

Descriptive statistics will be calculated to characterize and present the study population and baseline findings. Data normality distribution will be verified using the Shapiro-Wilk test. For normally distributed continuous variables, comparative analyses will be performed using Student’s *t-*test. Continuous variables that are not normally distributed will be compared using the Mann-Whitney *U* test. Group comparisons for nominal variables will be conducted using the Fisher exact test or the *χ*^2^ test, as deemed appropriate. Linear regression analysis with the baseline value of the outcome as a covariate will be used to compare the treatment groups. Log transformation will be performed in case of apparent violation of the normal distribution of the data. All tests will be two-tailed, and differences will be considered significant at the level of *p* ≤ 0.05. The number of missing data points will be presented for each variable. Nominal variables will be presented as *n* (% of the group). The outcomes will be presented as differences in medians for continuous data with non-normal distribution and as differences in means for data with normal distribution, both with a 95% confidence interval.

The clinical inference will be based on 95% confidence intervals for the regression coefficient for treatment effect. If the 95% confidence interval does not include 0, we will conclude that the difference between the treatment groups is clinically significant.

Data from the CBGM and CGM will be analyzed separately. To evaluate the capillary blood glucose levels at 30, 60, 90, 120, 150, and 180 min after the administration of the prandial bolus and the number of hypoglycemia episodes, data from the CBGM will be used. Data from CGM will be adopted to calculate the GR, PG, time to PG, MAGE, and time in the postprandial glucose range between 70 and 180 mg/dl (4.0–10.0 mmol/l).

The AUC will be calculated geometrically by applying the trapezoid rule. The incremental area under the blood glucose response curve (iAUC) is defined as the sum of all sensor excursions from the baseline value for the 3-h post-meal period. The positive AUC (pAUC) will be calculated based on the intersection points of the estimated curve with the baseline and integration of the area above the baseline.

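### The hypoglycemia count rests on meter readings 30 min apart plus symptom-triggered tests, so short asymptomatic lows can be missed, and no listed CGM outcome isolates lows

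*Protocol article*

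**What the plan says.** The End points section of the Protocol article makes the number of hypoglycemia episodes a secondary endpoint based on self-monitored glucose. The Statistical analysis section fixes the same source: "and the number of hypoglycemia episodes, data from the CBGM will be used". It also says that meter and sensor data are analysed separately.

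Under Study procedure, capillary glucose is measured "at 0, 30, 60, 90, 120, 150, and 180 min after insulin administration with a continuously working monitoring system". There are two further routes to a meter value:
- Symptoms: "Caregivers and patients will also be instructed to report symptoms of hypoglycemia with additional glycemia measurements".
- A retest once a low has been found and treated: "After 15 min, the glucose level must be controlled again".

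The definition asks for neither symptoms nor a minimum duration: "Hypoglycemia will be defined as the glucose level below or equal to 70 mg/dl".

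For the sensor, Statistical analysis states: "Data from CGM will be adopted to calculate the GR, PG, time to PG, MAGE, and time in the postprandial glucose range" of 70–180 mg/dl. End points adds AUC to that list. Neither section names a sensor-based count of lows or time at or below 70 mg/dl.

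**The concern.** Under the protocol's definition, any value at or below 70 mg/dl is hypoglycemia. A brief low without symptoms is therefore an event, but the count includes it only if a scheduled reading happens to fall inside it. The same section expects glucose to move quickly in this window: "There is a high possibility that rapid glycemic fluctuations will be observed after an h-GI meal".

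The Background section makes avoidance of late hypoglycemia part of the aim, and the Harms section names hypoglycemia as the most likely harmful effect after the meal. The comparison sets a bolus 50% larger, with basal insulin suspended, against the usual one. If events are under-counted, the trial has fewer of them on which to judge this question, and a finding of little difference could be taken as more reassuring than it is. The sensor records the same three hours, but the listed outcomes do not use it to isolate lows.

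**Working it through.** The article states no figure for the hypoglycemia endpoint. Its sample size of 72 concerns glucose at 90 min and has no bearing here. The check is how often the meter schedule meets a short low.

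**Inputs**
- Reading times 0, 30, …, 180 min, so the gap is g = 30 min (Study procedure).
- Threshold at or below 70 mg/dl, with no symptom or duration requirement (Study procedure).
- Duration D of one asymptomatic low: not in the article; 10, 15, 20, 25 and 30 min are assumed.
- No symptom-triggered test, because the low is asymptomatic by assumption. Meter error is ignored.

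**Step 1: capture by the schedule.** Let the low start at a uniformly random time within 0–180 min. It meets the next reading only if it starts in the last D minutes of a gap. Hence P(captured) = D/g for D < 30, and 1 for D ≥ 30.

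| D (min) | Captured | Missed |
|---|---|---|
| 10 | 10/30 = 33% | 67% |
| 15 | 15/30 = 50% | 50% |
| 20 | 20/30 = 67% | 33% |
| 25 | 25/30 = 83% | 17% |
| 30 or more | 100% | 0% |

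**Step 2: sensitivity to the placement assumption.** If only lows that both start and end inside the window are considered, P(captured) = 1 − 6(30 − D)/(180 − D):
- D = 10: 1 − 120/170 = 29.4%
- D = 15: 1 − 90/165 = 45.5%
- D = 20: 1 − 60/160 = 62.5%

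This version leaves out lows still in progress at 180 min, which the last reading would catch. D/30 is therefore the better figure for the whole window.

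**Step 3: effect on the comparison.** If the same share f of lows is captured on both days, true proportions p1 and p2 are observed as f·p1 and f·p2. The difference becomes f(p2 − p1), and the ratio p2/p1 is unchanged. Take assumed true proportions of 10% and 20%, with every low asymptomatic and 15 min long, so f = 0.5. The observed proportions are then 5% and 10%: the difference falls from 10 to 5 percentage points, the ratio stays at 2, and half the events remain to estimate it.

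**Step 4: the sensor.** The article gives no sensor interval. With an assumed reading every 5 min, any low of 5 min or longer contains a reading, so sampling alone would miss none of the durations above. Sensor error is not modelled. Time in 70–180 mg/dl does not replace a measure of lows: time outside that range is time below 70 plus time above 180. A bolus that cuts highs and adds lows by the same number of minutes leaves it unchanged.

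**The case against.** Using the meter is a consistent, prespecified choice, and End points and Statistical analysis agree on it. Sensor readings are less accurate at low glucose, which is a fair reason to prefer the meter. Both points stand: this is not a contradiction, and the meter count should remain.

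The loss concerns only lows that are both asymptomatic and shorter than 30 min. Snacks and meals are barred during the observation period, and glucose is given only when hypoglycemia is found, so an undetected low may well last until the next reading. This also stands, and it is why no overall share of missed episodes can be given.

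It can be said that the sensor is already used. Study procedure says "the blood glucose level can be checked with both the CGM and glucometer to obtain the highest accuracy of glycemic level", but that check is optional and tied to the specified time points. Harms uses the sensor together with the meter to guard against severe events, but no rule brings a sensor-detected low into the endpoint. This answers the point only in part.

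A reader might infer three stronger things that the article does not support:
- That short lows *are* missed. Some coincide with a scheduled reading, and symptoms will reveal others.
- That the protocol acknowledges asymptomatic lows in this window. Its remark on asymptomatic episodes concerns the nights before the test meals.
- That the relative comparison is pushed towards no difference. With equal capture on both days the ratio is preserved (Step 3). Capture might differ between boluses, but nothing in the article shows that it does, or in which direction.

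Finally, extra sensor measures are often left to an analysis plan. Here, however, the article itself fixes the data source for this endpoint and lists the sensor outcomes.

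**Conclusion.** The point holds as a limit on the sensitivity of a secondary safety endpoint. Asymptomatic lows shorter than 30 min can be missed, and the schedule captures about D/30 of them: 33%, 50% and 67% at 10, 15 and 20 min. Lows of 30 min or more are always captured. The figures rest on assumed durations and a random start; the article gives neither duration nor frequency, so the total loss could be small or substantial.

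The consequence is a lower event count, less precision and a smaller absolute difference on a question within the stated aim. The primary endpoint and the sample size are unaffected. The case for change is that better information is already being recorded and no listed outcome isolates it, not that the meter count is wrong.

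**What to change.** Keep the meter-based count as it is. In End points and Statistical analysis, add a supportive secondary sensor measure over 0–180 min after the bolus:
- minutes at or below 70 mg/dl; and
- number of episodes at or below 70 mg/dl, with a minimum duration fixed in advance so that one stray sensor value is not an event.

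Compare both within participant between the Super Bolus and Normal Bolus days, and report them beside the meter count. State how many participants lack sensor data: the Compliance section says that only meter data are analysed after a CGM failure, so the new measure will be missing for them. Fix the definitions before unblinding.

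The cost is a small extra analysis of records already downloaded, plus the registry entry and ethics committee notice that the Monitoring section requires for a change. No procedure or treatment changes. The downsides are lower sensor accuracy at low glucose and some missing sensor data, which is why the measure should support the meter count and not replace it.

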### Harms

We do not expect any severe complications during the study. The medical equipment and insulin used during the study will be approved for clinical use. The most probable and harmful adverse effect during the postprandial period is hypoglycemia. Intensive glycemic control using both CGM and SMBG will be used against severe hypoglycemic events and will provide the most accurate glycemic measurements. Despite the inconvenience of having to monitor the blood *glucose levels by doing* multiple finger *pricks, it is necessary to ensure the safety of the study procedure. Moreover, CGM-related minor local adverse events, such as the possibility of developing an infection*, redness, *bleeding*, hypersensitivity, itching, irritation, or pain at the sensor site, may occur. CGM will be applied by qualified personnel to reduce the risk of complications. Data concerning all harms will be gathered and reported as indicated in the Consolidated Standards of Reporting Trials (CONSORT) extension on harms document [27]. Any adverse events will also be reported in the individual patient’s CRFs.

All serious adverse events will be immediately reported to the project leader who will be responsible for notifying the ethics committee and all participating investigators. If any serious adverse events occur during the study procedure, financial compensation will be covered by the grant.

## Discussion

According to the ISPAD Guidelines, low-GI products are recommended for diabetic patients to alleviate glycemic variations [20]. Meals with the same CHO content but different GIs produce clinically significant changes in a person’s postprandial glycemic excursions, as proven in a controlled study among children with T1D that showed that substituting a diet with high-GI foods with a diet comprised of low-GI foods improved glycemic control after 12 months [20].

Some strategies may be implemented to reduce the average GI of meals. The addition of a moderate amount of protein, healthy fats (monounsaturated fatty acids [MUFA] and polyunsaturated fatty acids [PUFA]), or dietary fiber to a meal containing predominantly CHOs may assist in reducing postprandial hyperglycemia [20]. A meal-time schedule, the routine period when food is offered and available without snacking in between meals, may contribute to the optimal control of postprandial glycemia [20].

Adjustment of the type and dose of insulin for h-GI meals remains a challenge. According to Dżygało et al., neither of the two insulin analogs, glulisine nor aspart, provide a stabilized glycemic profile after an h-GI meal [28]. The new formulation of faster-acting insulin aspart (faster aspart) has a more rapid onset of appearance and greater early exposure in comparison with aspart for children and adolescents. Using this new formulation, a statistically significant reduction of 2 h for postprandial glycemia after a standardized meal was reported [29, 30]. However, due to regulatory approval and availability, its common use in clinical practice is limited. Lujif et al. demonstrated that the administration of prandial rapid-acting insulin analogs 15 min (instead of 30 min) before a meal, directly at the start of eating, resulted in a lower rate of PPH without an increased risk of hypoglycemia [21]. Therefore, we decided to deliver an insulin bolus 15 min before a meal. O’Connel et al. tested two types of prandial bolus for an h-GI meal: a normal bolus (given over 3 min before the meal) vs dual (50:50% over 2 h) and found no difference between them [10]. Regardless of the bolus type, high glycemic excursions were still observed, with a mean glycemic rise of + 95.4 mg/dl compared to the baseline [10]. An additional dose of insulin was also considered as a possible solution for the h-GI meals issue. Groele et al. compared the dose of prandial insulin calculated based on the individual patient’s ICR with the dose increased by about 30% for an h-GI meal and concluded that the frequencies of PPH and hypoglycemia were similar in both groups, but the additional dose of insulin significantly reduced glucose excursion in terms of the mean postprandial glycemia (47.4 ± 39.8 mg/dl vs 76.2 ± 58.2 mg/dl) [22]. We know that a dose of insulin increased by 30% does not cause a higher incidence of hypoglycemia episodes and leads to lower postprandial glycemia, but the incidence of hyperglycemia episodes still remains unsatisfactory. Therefore, we decided to conduct this study based on the Super Bolus idea to achieve a reduction in the frequency of PPH, with a simultaneous decrement in glycemic rise and hypoglycemia episodes. The available pertinent literature only refers to in-silico studies and clinical practice [23, 24]. We defined a Super Bolus as a boost of prandial insulin (increased by 50% in comparison with the dose calculated based on individualized patient’s ICR) and a simultaneous suspension of the basal insulin for 2 h. During that time, the insulin is still acting, and 2 h seems to be a short period for a rebound effect. Moreover, our patients reported the best experience with the above-mentioned combination.

A comprehensive and effective solution to this huge and frequent clinical difficulty of PPH after an h-GI meal has not yet been found. The problem is known and important, and the presented solution is innovative and easy to apply in everyday life.

In conclusion, the findings of this randomized controlled aim to show that pediatric patients report the best experience with a combination of a Super Bolus—the 50% increase in prandial insulin dose in comparison with the dose calculated based on the individualized patient’s ICR—and a simultaneous suspension of basal insulin for 2 h. This study will contribute to the formulation of better recommendations on the use of Super Bolus to address problems concerning PPH after an h-HI meal in children with T1D.

### Trial status

Recruitment started in January 2020 and is planned to end in July 2022, with all patients randomized. The current protocol version was 2.0, dated August 30, 2020.

## Data Availability

The full protocol will be freely available because of open-access publication. The findings of this randomized controlled trial will be submitted to a peer-reviewed journal. Abstracts will be submitted to relevant national and international conferences. Standards from the guidelines of the Consolidated Standards of Reporting Trials will be followed for this trial. All investigators will have access to the final trial dataset.

## Abbreviations

PPH: Postprandial hyperglycemia
T1D: Type 1 diabetes
h-GI: High glycemic index
AUC: Area under the blood glucose curve
MAGE: Mean amplitude of glycemic excursion
ICR: Insulin-carbohydrate ratio
CHO: Carbohydrate
SuBo: Super Bolus
NoBo: Normal bolus
CGM: Continuous glucose monitoring system
SMBG: Self-monitoring of blood glucose
GI: Glycemic index
GL: Glycemic load
GR: Glycemic rise
PG: Peak glucose level
SDBG: Standard deviation of blood glucose
CRF: Case report form
DSMB: Data and Safety Monitoring Board
iAUC: Incremental area under the blood glucose curve
pAUC: Positive AUC
CONSORT: Consolidated Standards of Reporting Trials
